# Pioglitazone in spontaneous subarachnoid hemorrhage: study protocol of a multicenter, double-blind, randomized trial (PSSH)

**DOI:** 10.3389/fphar.2023.1323292

**Published:** 2024-01-05

**Keywords:** clinical trial, pioglitazone, SAH, PPARγ, neuroprotection

**Clinical Trial Registration:**
clinicaltrials.gov, identifier ChiCTR2200062954.

## Introduction

Subarachnoid hemorrhage (SAH) is a condition that often occurs in people who have cerebral vascular disease and is hallmarked by increased morbidity and mortality rates and a poor prognosis, particularly in patients who have hypertension. There have been reports indicating that the incidence rate of SAH ranges from 6.2 to 10 cases per 100,000 people in the West (Korja et al., 2016; Mackey et al., 2016; Etminan et al., 2019) and affects approximately 600 000 patients worldwide (Feigin et al., 2009). SAH is associated with a high overall mortality rate that may reach as high as 67% (Nieuwkamp et al., 2009), and only a third of survivors remaining live dependently (van Gijn et al., 2007). Since SAH results in a significant loss of production and resources, it places a considerable cost on society (Zolnourian et al., 2020).

Many previous scholars have attempted to improve outcomes after SAH, and statins (Kirkpatrick et al., 2014; Naraoka et al., 2018), magnesium (Dorhout Mees et al., 2012), and tranexamic acid (Post et al., 2021) are among the medications that have demonstrated superior neuroprotective benefits in basic research; nonetheless, these efforts to enhance outcomes after SAH have primarily been unsuccessful. Although numerous studies have shown that statins or clazosentan may significantly alleviate cerebral vasospasm (CVS), these medications have little impact on the outcomes after a SAH (Macdonald et al., 2011; Chen J. et al., 2020). Despite significant advancements in methods for producing aneurysms, long-term outcomes have not been improved, and there is a lack of medical therapy that is suited for the condition.

Red blood cells and lysis products in subarachnoid space or brain tissue may produce a significant inflammatory response along with a rise in levels of oxyhemoglobin, endothelin, nitric oxide, and proinflammatory cytokines, resulting in early brain injury (EBI) and CVS and ultimately leading to neurological dysfunction and death after SAH (van Gijn and Rinkel, 2001; Chen et al., 2016; Ch et al., 2018; Chen et al., 2019a; Chen J-H. et al., 2020). Therefore, finding a way to prevent CVS and EBI should be the primary objective of any novel pharmacological therapy for SAH. Pioglitazone is a drug that has been approved by the FDA as a peroxisome proliferator-activated receptor-gamma (PPARγ) agonist. PPARγ is a nuclear hormone receptor, and its activation regulates many aspects of inflammatory processes as well as mitochondrial homeostasis. PPAR-γ agonists can block the generation of pro-inflammatory mediators and nitric oxide by inhibiting the activation of astrocytes and microglia (Storer et al., 2005); Additionally, Oxidative stress and mitochondrial biogenesis are regulated by the transcriptional factor, PPAR-γ coactivator 1-α (PGC-1α) (Eschbach et al., 2015). Animal studies have proven that Pioglitazone or PPAR-γ exerts neuroprotective benefits in multiple disorders of the central nervous system (CNS), however, the specific neuroprotection pathways of PPAR-γ agonists/Pioglitazone are still obscure (Zuhayra et al., 2011; Pilipović et al., 2015; Liang et al., 2022). Animal models of Parkinson’s disease treated with a dosage of pioglitazone equivalent of the human FDA-approved dosage demonstrated both effective CNS penetration of pioglitazone and neuroprotection benefits (Kernan et al., 2016; Pinto et al., 2016). Nevertheless, it is yet unknown whether or not Pioglitazone has any neuroprotective benefits following SAH in humans.

Thus, the focus of the proposed clinical study is to examine the effectiveness and safety of pioglitazone in treating SAH.

## Methods/design

### Study design

This multicenter, double-blind, placebo-controlled, parallel-group, randomized clinical trial will be conducted in the 904^th^ Hospital of Joint Logistic Support Force of PLA (Wuxi Taihu Hospital), Renmin Hospital of Wuhan University, The Second Affiliated Hospital of Tianjin Medical University, The Second Affiliated Hospital of Nanchang University.

### Patient and public participation

Patient and public involvement Patients and/or the public did not participate in any stage of the design, execution, reporting, or distribution of the plans of this study.

### Ethical considerations and informed consent

The researcher or other authorized personnel will obtain written informed permission from each patient or respective family member or guardian after explaining the benefits and risks of participating in the research. This trial has received the written approval of the Medical Ethics Committee of 904^th^ Hospital of Joint Logistic Support Force of PLA (Wuxi Taihu Hospital, No. 20220701), and other Sub-centers. The principles outlined in the Declaration of Helsinki, which were developed by the World Medical Association, have been adhered to throughout the execution of this project.

### Qualifications for participating centers

The researchers will cooperate with four medical centers in various parts of China (north, south, east, and central China). Each facility is equipped with over two referral units and has a skilled treatment team who has experience in diagnosing SAH and providing effective treatment. As a result, it is generally accepted that this cohort is capable of providing an accurate representation of the population at both the regional and national levels. All participants in this trial will be monitored and treated at one of the collaborating medical centers throughout the study.

### Study participants

Participants for this research will be selected from SAH patients currently being treated at any of the four hospitals. Participants will be recruited consecutively across all of the clinical facilities. The patients will be selected using specified eligibility requirements, and then the competent authority will randomly assign them to one of the treatment groups.

#### Inclusion criteria

To be eligible for inclusion in the study, patients must satisfy all of the following conditions.1. Ranging in age from 18 to 70 years2. Head CT evidence of SAH.3. CTA, MRA, or DSA confirmed the presence of an intracranial aneurysm as the cause of the patient’s recent SAH.4. The time between SAH onset and admission should not exceed 24 h.5. The patient’s caregiver must agree to the research protocol and sign an informed consent form as per the guidelines set out by the ethics committee.

#### Exclusion criteria

1. Symptoms consistent with SAH lasting more than 3 days before admission2. The CT scan shows a pattern of hemorrhage consistent with a traumatic SAH.3. Patients addicted to drugs4. Patients with chronic renal failure that requires treatment with dialysis5. Patients with a life expectancy of fewer than 6 months due to a severe terminal illness6. Severely coagulation dysfunction patients7. Patients with organ failure8. Individuals suffering from severe psychosomatic illness9. Pregnant or lactating women10. The caregiver responsible for the patient declined to provide permission for the patient to take part in this experiment.11. The patient was enrolled in a different randomized controlled trial (RCT) aimed at treating SAH.12. Patients who had taken rosiglitazone or pioglitazone within the previous 90 days prior to randomization13. Current participation in a conflicting clinical trial. A conflicting clinical trial is defined as a trial with any of the following:(1) Intervention that is known to affect the incidence of stroke or myocardial infarction(2) An experimental pharmacological intervention(3) Stroke as a possible outcome(4) Exclusion for participation in another trial14. Clinically significant structural brain disease that the investigator believes would interfere with study evaluations15. Symptoms of congestive heart failure in the past16. Known intolerance to rosiglitazone or pioglitazone17. Diabetes Mellitus, Type I or II18. Previous Bladder Cancer History19. Evidence of a previous case of macular edema20. Individuals subject to temporary exclusions are eligible for enrollment after their status has stabilized. The temporal exclusions include those with:(1) Over 2.5 times the standard upper limit for alanine aminotransferase (ALT)(2) Below 8.5 g/dL of hemoglobin(3) Pitting edema of the feet and legs, mild to severe (IRIS grade 3 or 4)(4) Scheduled carotid surgery or carotid stenting (delaying randomization till 2 weeks after the operation)

### Randomization

A statistician will use a random number generator to assign a number to each of the 400 participants based on the time they were admitted. The participants will be randomized to either the pioglitazone group or a placebo control group.

### Blinding and emergency unblinding

The treatment plan that will be administered to each participant will be developed using a randomized allocation sequence and then put in numbered, opaque envelopes that have been sealed. The blinded codes will be preserved by the drug administrator. In the case that a patient has a severe adverse reaction and it is essential to promptly establish the drug that was administered, a primary investigator from the research unit will open the envelope containing that patient’s information. The participation of the patient in the experiment will be discontinued as soon as the data have been unmasked. The findings will be communicated to the clinical research associate. The unmasking will be documented, along with the cause for it and the date it took place, and the researchers will sign the case report form.

### Interventions

Patients in both groups will be given standard therapies, which may include sedation, absolute bed rest, maintaining fluid balance, and hemostasis. Pioglitazone group: Patients will also be given an oral dosage of pioglitazone (approval No. GYZZ J20090134; Tianjin Taketian Pharmaceutical Co. LTD, Tianjin, China) in addition to standard care. Patients were allocated to receive a starting dosage of 15 mg of pioglitazone titrated to reach a targeted dosage of 45 mg daily. Placebo control group: patients will get placebos orally (starch tablets with the same appearance as atorvastatin) in addition to their standard therapies. The recommended dose will be the same as for pioglitazone. The trial’s workflow is depicted in Figure 1.

**FIGURE 1 F1:**
[figure not shown]
Flow chart of the trial.

### Procedures

At admission to the hospital, all patients underwent baseline cranial CT and CT angiography (CTA) or DSA to confirm the diagnosis of SAH. Then, investigators recorded sex, age, Fisher Grade Score, Glasgow Coma Scale, Hunt-Hess Scores, *etc.* for each patient. The investigators completed the enrollment assessment and random allocation as soon as possible. Following random assignment, those in the intervention group were started on the therapy immediately.

### Outcome measures

#### Primary outcomes

Clinical outcome at 6 months and 12 months post-randomization is the primary endpoint measure evaluated using the modified Rankin Scale (mRS) through a standardized interview (Wilson et al., 2005). Research physicians blinded to treatment assignment performed all evaluations. Medical doctors conducting research were instructed on how to undertake the structured face-to-face interview to calculate the mRS score as per standard operating procedures (SOPs). Clinical outcomes were classified as good (mRS 0–3) or poor (mRS 4–6) after the scores were recorded.

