### Follow-up

The follow-up duration will be 6 months and 12 months beginning from the time when patients were randomized. Patients will be contacted by phone and asked to come back to the hospital for further examinations, which will include conventional CT scans, transcranial Doppler ultrasonography, and neurological scale evaluations. If a patient cannot be located for follow-up, the most recent data evaluated will be used to determine the patient’s values for the 6-month follow-up (Table 1).

**TABLE 1 T1:** Outcome measures and measurement points.

Visit number	Screening period	Follow-up period		
	1	2	3	4
Research arrangement	Screening	In-hospital	30 days	6 months
Informed consent	√			
Selection criteria	√			
Baseline information	√			
General history	√			
Symptoms and physical examination	√			
GCS grading	√			
WFNS grading	√			
Hunt-Hess grading	√			
Conventional brain CT	√	√		
Transcranial Doppler	√	√		
Electrocardiogram	√	√		
Blood sugar	√	√		
Blood NT-proBNP	√	√		
All-cause mortality			√	
mRS score			√	√
Mo-CA			√	√
End point evaluation		√	√	√
Adverse event evaluation		√	√	√
Complications		√	√	√
Intensive care unit stay		√	√	√
Length of hospital		√	√	√
Hospitalization costs		√	√	√

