### Data monitoring body and management

This research will be carried out in compliance with the guidelines for good clinical practice as well as the principles outlined in the Declaration of Helsinki. An independent clinical trial data management committee (CTDMC) composed of members of the ethics committee, neurosurgeons, physicians, information specialists, and intensivists will complete non-blinded evaluations of all of the patients’ effectiveness and safety data independently, comprising AEs and dropout rates, recorded from the time of informed consent to 180 days after the randomization process. The CTDMC is responsible for the examination and analysis of clinical data and holds regular meetings to control the quality of the trials.

The patient’s health records will be digitized and stored on a computer, and the data will be uploaded to the Electronic Data Capture system (ResMan, www.medresman.org). Details provided on the case data form will be checked for accuracy. Any changes or corrections made will retain a clear record of the original. When an amendment or correction is made, the researcher will note the date, sign their name, and provide an explanation (if required). All of the patient’s medical history, including any alterations, deletions, or updates, will be stored digitally. The audit trail will be secured in a way that prevents any unauthorized changes or deletions. The clinical data management system will have authority management such that only authorized personnel will be allowed to operate it. Electronic signatures are widely used in ERMs (electronic management systems). To ensure the privacy and security of the collected clinical data, only authorized users will be able to access the system and enter, modify, or view the data. All documentation shall be kept for at least 5 years following the conclusion of the experiment, as required by the China Drug Clinical Trial Management Specification.

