### Sample size estimates

According to previous clinical data and our pilot study’s preliminary experiments, 51.9% (42/81, retrospective data) of patients in the untreated group had a good clinical outcome compared with 63.3% (19/30) in the intervention group. The decision to recruit 378 patients (189 in each arm) was based on a power analysis with an alpha of 0.05, a statistical power of 80%, and a 10% loss to follow-up. We decided to enroll 400 patients (200 in each arm). All of the data from the study’s baseline as well as its outcomes were input into the database by a research nurse. The analysis of the data was performed by the research coordinator. The CTDMC checked the data and discussed the findings.

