### Statistical analysis

SPSS 20.0 will be utilized for the analysis of all the data. Measurement data will be expressed as the mean ± SD. After the first half of the patients were recruited, CTDMC evaluated the safety of the trial participants, efficacy, and overall progress of the study and did a masked interim analysis. All patients assigned a random number during the randomization process will be examined using an intention-to-treat analysis. If any measurements in the medical records or outcome measures are found to be incomplete during the statistical analysis, the final data obtained will be considered the final result for use in the statistical analysis.

Two-sample t-tests and odds ratios (OR) with 95% confidence intervals (CI) are provided to identify variations across treatment groups. The criterion for statistical significance will be set at *p* < 0.05. Adjusted odds ratios (aORs) will be calculated using multivariate logistic regression to account for the impact of the treatment facility and any variations in baseline variables for the primary and secondary outcomes. We also did per-protocol and as-treated analyses.

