## Discussion

This protocol describes the PSSH study, which will be the first large sample multicenter project to prospectively examine the effectiveness and safety of Pioglitazone in patients with aSAH, from hospital admission to 6 months follow-up. If it succeeds, it might help patients with SAH in the long term, giving them hope despite their complicated neurocognitive symptoms and disabilities. It also has important clinical translational value.

In aSAH patients, neuroinflammation occurs shortly after the bleeding and is associated with EBI, delayed cerebral ischemia, poor functional outcome, and case fatality (Chen et al., 2021). Inhibiting microglial and astrocyte activation with PPAR-γ agonists reduces the release of pro-inflammatory mediators and nitric oxide (Storer et al., 2005). Our earlier experimental SAH investigation found that PPAR-γ upregulation after SAH may ameliorate neurological dysfunction and alleviate EBI (Chen et al., 2019b). As a result, PPAR-γ agonists (Pioglitazone) may emerge as a safe and successful means of treating aSAH. Pioglitazone may be an important target to reduce EBI and improve the long-term outcome after aSAH.

Pioglitazone’s most frequent side effects are dosage-dependent and include nausea, vomiting, edema, and myopathy, all of which improve after the medicine has stopped being taken by the patient. Pioglitazone has a low incidence of side effects, and it has an excellent safety and tolerability profile with no known safety concerns. (Dormandy et al., 2005; Belfort et al., 2006).

Nonetheless, we believe that a well-designed large sample multicenter trial could help us better understand the value of Pioglitazone in aSAH patients. Our study’s findings might have significant significance for patient care in clinical settings.

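### Two unranked primary time points (mRS at 6 and 12 months) with no success rule leave the 5% error rate unsecured, and Table 1 omits the 12-month assessment that the text requires

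*Protocol article*

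**What the plan says.** The Primary outcomes section of the Protocol article sets the endpoint: "Clinical outcome at 6 months and 12 months post-randomization is the primary endpoint measure evaluated using the modified Rankin Scale (mRS"). The scale is then split in two: "Clinical outcomes were classified as good (mRS 0–3) or poor (mRS 4–6) after the scores were recorded". Neither time point is placed above the other, and no rule says whether success needs one or both. The Abstract names mRS as primary without giving a time.

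The Statistical analysis section has one general threshold, "The criterion for statistical significance will be set at" p < 0.05, with no split, order or both-must-succeed condition. The Sample size estimates section describes "a power analysis with an alpha of 0.05, a statistical power of 80%, and a 10% loss to follow-up". It rests on one contrast: "51.9% (42/81, retrospective data) of patients in the untreated group had a good clinical outcome", against 63.3% (19/30) with the intervention. The time point of these rates is not given.

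On how long patients are followed, the article says different things:

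- Follow-up, prose: "The follow-up duration will be 6 months and 12 months beginning from the time when patients were randomized".
- Follow-up, Table 1: the last column is visit 4 at 6 months. mRS is ticked at 30 days and 6 months, and there is no 12-month column.
- Data monitoring body and management: the committee reviews efficacy and safety data "recorded from the time of informed consent to 180 days after the randomization process".
- Discussion: patients are studied "from hospital admission to 6 months follow-up".

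**The concern.** There are two separate problems, and both concern the primary endpoint.

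The first is the decision rule. With two primary results and one threshold, the trial could be read as positive if either result crosses it, or only if both do. These are different trials with different error rates and different power. If the choice stays open until the results are known, the more favourable reading can be taken.

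The second is data collection. Site staff usually work from the schedule of assessments. Here the schedule stops six months before the second primary assessment that the text requires. An analysis plan can supply a testing rule later, but it cannot recover a visit that was not made.

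**Working it through.** **Inputs.** Good-outcome rates p1 = 0.519 and p2 = 0.633, alpha 0.05, power 80%, loss 10% and 200 per arm, all from Sample size estimates. Evaluable patients per arm: 200 × 0.9 = 180. Two assumptions are needed. The tests are taken as two-sided, since the article does not give sidedness. The correlation ρ between the 6- and 12-month test statistics is not given, so a range is shown.

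**The plan's own figure first.** The stated requirement is 189 per arm including loss. With d = 0.633 − 0.519 = 0.114 and mean rate 0.576:

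n = [1.96 × √(2 × 0.576 × 0.424) + 0.8416 × √(0.519 × 0.481 + 0.633 × 0.367)]² / 0.114²
= (1.370 + 0.584)² / 0.012996 ≈ 294 per arm, and 294 / 0.9 ≈ 327 with loss.

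One-sided, the figures are 232 and 258. The figure of 189 is not reproduced. That is a separate issue and nothing below depends on it. It matters here only because the power figures start well under 80%.

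**Error if either time point may win.** Error = 1 − P(|Z1| < 1.96 and |Z2| < 1.96), with (Z1, Z2) bivariate normal with correlation ρ. Under independence this is 1 − 0.95² = 0.0975. The error if both must be significant follows as 0.05 + 0.05 − (either).

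| ρ (assumed) | Either may win | Both required |
|---|---|---|
| 0 | 9.75% | 0.25% |
| 0.5 | 9.1% | 0.9% |
| 0.7 | 8.3% | 1.7% |
| 0.8 | 7.8% | 2.2% |
| 0.9 | 7.0% | 3.0% |
| 0.95 | 6.5% | 3.5% |

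These count false positives in either direction. For a false claim of benefit alone, the nominal 2.5% becomes 4.5% at ρ = 0.5 and 3.2% at ρ = 0.95.

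**Power under each rule, 180 per arm, planned effect.** Let s0 = √(0.488448/180) = 0.0521, s1 = √(0.48195/180) = 0.0517 and b = (0.114 − z × s0)/s1.

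- One time point at 0.05: z = 1.96, b = 0.230, power 59.1%.
- One time point at 0.025 (Bonferroni): z = 2.241, b = −0.053, power 47.9%.
- Both required at 0.05, same effect at each time: P(both exceed) is 42.9% at ρ = 0.5, 46.8% at 0.7, 49.1% at 0.8, 52.1% at 0.9 and 54.2% at 0.95.

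Relative to a single test, a Bonferroni split costs 59.1 − 47.9 = 11.2 percentage points. Requiring both costs between 59.1 − 54.2 = 4.9 and 59.1 − 42.9 = 16.2 points.

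**Follow-up, side by side.** Two places require a 12-month assessment: Primary outcomes and the prose of Follow-up. Three stop at 6 months: Table 1, the 180-day window and the Discussion. Table 1 carries the most weight, because it is the operational list of what is measured when.

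**The case against.** The strongest defence is that this is a condensed article. Testing order and alpha allocation are commonly left to an analysis plan, which may exist, so a missing multiplicity rule is not in itself a fault. That stands. What remains is what the article does fix: two primary time points without rank, and a schedule that disagrees with them.

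Four stronger readings are tempting, and the article does not support them.

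- *That the error rate is inflated.* Nowhere does it say that one time point is enough. If both were required, the error would be at or below 5% with no adjustment. The inflated figures hold only under the either-may-win reading.
- *That the 12-month endpoint is unscheduled.* The Follow-up prose sets 12 months and calls patients back for neurological scales. The defect is a conflict between text and table.
- *That the missing-data rule covers only 6 months.* The sentence under Follow-up names only the 6-month value, but Statistical analysis has a general rule that takes the last data obtained for any incomplete outcome measure. That covers a missing 12-month mRS, although filling the gap with an older score is not the same as making the assessment.
- *That the two time points cause the low power.* The 59.1% for a single test arises from the sample size calculation. Only the further drop belongs here.

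Two of the three places that stop at 6 months are also weaker evidence: a committee's review window may end before the last outcome visit, and a Discussion sentence is only a summary. Table 1 has no such explanation.

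**Conclusion.** The point holds in this form: the primary endpoint is fixed ambiguously, so control at 5% is not secured, and the article contradicts itself on whether a 12-month assessment takes place.

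The size depends on the reading. Under either-may-win, the error is about 6.5% to 9.1% for ρ from 0.95 to 0.5, with 9.75% as the value under independence. Under both-required, the error is controlled, and power for the planned effect at 180 per arm falls from 59.1% to between about 43% and 54%, assuming the same effect at both times. The correlation and the two-sided tests are assumptions.

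The schedule conflict needs no assumption. It would cost one of the two primary assessments wherever Table 1 is followed as printed.

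**What to change.** Before any comparative outcome data are seen, choose one of these:

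1. Name one primary time point for mRS 0–3 and make the other secondary. Six months is the one that agrees with Table 1, the 180-day window and the Discussion, but the choice is the sponsor's.
2. Keep both in a fixed sequence: test 6 months at 0.05, and test 12 months at 0.05 only if the first is significant.

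Either option holds the error at 5% and needs no extra patients for multiplicity. A Bonferroni split would also control the error, but at the loss of about 11 points of power shown above.

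Then state which time point the 51.9% and 63.3% refer to, add a 12-month mRS column to Table 1, and reconcile the Follow-up, Data monitoring and Discussion sections with the chosen follow-up.

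The cost is protocol wording and one table column. The downside is that 12 months loses co-primary status or, in a sequence, can be claimed only after success at 6 months. The shortfall from the stated 80% power needs its own correction.
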